### Number of subjects

A total of 178 subjects will be randomized in a 1:1 ratio between the experimental and control arms.

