### Randomization

A unique feature of the ATLAS/NOA-29 trial is the intraoperative randomization process. Patients with imaging evidence suggestive of newly-diagnosed glioblastoma confined to the anterior temporal lobe will undergo craniotomy, typically performed as a pterional or temporal craniotomy, to allow for both temporal GTR and ATL. Once the dura is opened and tumor access is achieved, tumor tissue will be sent for frozen section analysis by the neuropathologist or pathologist in charge. Randomization will only occur after the (neuro)-pathologist has confirmed the diagnosis of diffuse high-grade glioma based on the frozen section results. The frozen section procedure, as performed in this study, is expected to prolong the surgery by approximately 10 to 20 min.

Randomization will be performed using the method of permuted blocks with variable block sizes. The randomization number will be assigned through the electronic case report form (eCRF) system, in a 1:1 ratio between the experimental (ATL) and control (GTR) interventions. Stratification will occur based on two criteria: age group (< 50 years or ≥ 50 years) and pre-operative KPS (70–80% vs. 90–100%).

Blinding of the surgical procedure is not feasible due to its inherent nature. The operating neurosurgeon and other treating physicians must review MRI scans during follow-up examinations, which will reveal the surgical approach. Consequently, the randomization process must be open.

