## Statistics and analysis

### Sample size calculation

The sample size calculation is based on the primary endpoints of OS and QoL, with equal allocation of subjects to the two treatment groups. Assuming a two-sided alpha level of 5%, median OS times of 17 months in the control group and 27.5 months in the experimental group, a 3-year accrual period, and a 3-year follow-up period (resulting in a total trial duration of 72 months), a total of 170 subjects with a confirmed diagnosis of glioblastoma will provide 80% power to test the null hypothesis of equal OS between the two groups (two-sided log-rank test). The assumed survival benefit of a 10-month improvement with ATL over GTR is based on existing data from retrospective glioblastoma surgery studies involving ATL [16, 25] as well as analyses of EORTC datasets that are not specific to temporal tumor localization [9].

It is anticipated that approximately 4.5% of randomized patients will not have glioblastoma CNS WHO grade 4 but rather a different subtype of diffuse high-grade glioma, as determined by the final integrated histopathological and molecular diagnosis according to the 2021 WHO classification [55]. If the final diagnosis does not confirm glioblastoma IDH wildtype (CNS WHO grade 4), these patients will remain in the trial for safety follow-up but will be replaced in their respective groups and excluded from the mITT population. This replacement strategy will result in a maximum of 178 randomized patients. All randomized patients, regardless of diagnosis, will undergo regular follow-up as outlined in the trial protocol for safety monitoring.

The two primary endpoints will be analyzed in a hierarchical order, with QoL being tested for non-inferiority in the experimental group compared to the control group if the null hypothesis for OS is rejected. QoL measurements will be conducted quarterly, and a prior study demonstrated an approximately linear time dependence of the QoL (= global health) score on time [49].

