### Primary outcome

The statistical analysis will be conducted at the Study Center Bonn (SZB) of the University of Bonn Medical Center under the direction of [name]. [name]. The primary, confirmatory analysis will compare OS between the treatment groups using a two-sided log-rank test at a significance level of 5%. This analysis will be performed on the mITT population. The log-rank test will be stratified by age group (< 50 years or ≥ 50 years) and pre-operative KPS class (70–80% vs. 90–100%). Surviving patients and those lost to follow-up will be censored at the respective time points. OS will be summarized using Kaplan–Meier curves, with median survival estimates and corresponding 95% confidence intervals reported.

A sensitivity analysis for OS will be conducted using a Cox proportional hazards model with treatment group and MGMT promoter methylation status (hypermethylated vs. unmethylated) as independent variables. If the MGMT promoter methylation status is not available, missing data for these patients will be imputed. In another sensitivity analysis for OS, a Cox proportional hazards model with treatment group and center recruitment volume (high vs. low) will be fitted. Additionally, potential prognostic factors, including age, preoperative KPS, MGMT promoter methylation status (hypermethylated vs. unmethylated), and center recruitment volume (high vs. low), will be analyzed using a multivariate Cox proportional hazard model for OS.

If OS of ATL significantly differs from that of GTR, the patient-reported QoL domain "global health status" from the EORTC QLQ-C30 questionnaire will be analyzed as a co-primary endpoint. Changes from baseline in the experimental arm (ATL) will be compared to the standard arm (GTR) to assess non-inferiority, using a non-inferiority margin of 1.6 score points per year. This evaluation will be performed on the mITT population and using a linear mixed-effects model (QoL score as dependent variable, random patient intercept, treatment group + time as independent variables, estimating a 95% confidence interval of the interaction between time and treatment).

Overall superiority of ATL will require significantly prolonged OS alongside non-inferiority in the development of global health status over time. Due to the hierarchical testing approach, no adjustment of the type I error rate is necessary.

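### The two Cox sensitivity models that estimate the treatment effect on OS leave out the age and KPS strata of the primary log-rank test, and the model that has age and KPS does not name treatment

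*Protocol article*

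**What the plan says.** The Randomization section of the protocol article says "Stratification will occur based on two criteria": age below 50 versus 50 and over, and pre-operative KPS 70–80% versus 90–100%. The Primary outcome section carries both factors into the confirmatory test: "The log-rank test will be stratified by age group", and by KPS class with the same cut-offs. OS is to be summarised by Kaplan–Meier curves and medians with 95% confidence intervals.

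The same section then describes three Cox models for OS:

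- "A sensitivity analysis for OS will be conducted using a Cox proportional hazards model with treatment group and MGMT promoter methylation status", these two being the independent variables;
- as a further sensitivity analysis, "a Cox proportional hazards model with treatment group and center recruitment volume (high vs. low) will be fitted";
- a multivariable model of potential prognostic factors, listing age, preoperative KPS, MGMT status and centre volume. The list is open-ended and treatment group is not in it.

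These analyses are to be repeated in the ITT and per-protocol populations.

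**The concern.** A sensitivity analysis is easiest to read when it changes one element of the primary analysis. The two models that contain treatment change two: they add MGMT or centre volume, and they drop age and KPS.

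MGMT status is not a randomisation stratum, so the MGMT model is the planned check on whether a chance imbalance in MGMT explains the OS result. If its answer differs from the primary one, the reader cannot tell whether MGMT or the missing strata caused the difference. If the two agree, the two changes may simply have offset each other. The same ambiguity passes to the ITT and per-protocol repeats. Read literally, no planned treatment hazard ratio accounts for either randomisation factor.

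**Working it through.** **1. The plan's own figure.** The inputs are in the Sample size calculation section: "median OS times of 17 months in the control group and 27.5 months in the experimental group", 36 months of accrual, 36 months of follow-up, two-sided 5% and 80% power.

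- Hazard ratio under exponential survival: 17/27.5 = 0.618.
- Events (Schoenfeld): 4 × (1.960 + 0.842)² / (ln 0.618)² = 4 × 7.849 / 0.2313 = 135.7, so 136.
- Event probability: 1 − [exp(−λF) − exp(−λ(A+F))]/(λA), with λ = ln 2/median and A = F = 36. This gives 0.879 (control) and 0.735 (ATL), mean 0.807.
- N = 136/0.807 = 168.5, so 169. At N = 170 there are 170 × 0.807 = 137.2 expected events and the power is 80.4%.

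The stated 170 patients and 80% power are reproduced. Nothing below changes them.

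**2. The four OS analyses side by side.**

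| Analysis | Treatment | Age, KPS | Other factor |
|---|---|---|---|
| Log-rank test (primary) | yes | strata | none |
| Cox sensitivity 1 | yes | not stated | MGMT |
| Cox sensitivity 2 | yes | not stated | centre volume |
| Multivariable Cox | not named | covariates | MGMT, centre volume |

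No row with treatment differs from the first row in a single element.

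**3. Size.** The documents give no prognostic effects or prevalences, so this is a simulation on assumptions: 85% aged 50 or over, 40% with KPS 70–80, 40% MGMT-methylated, a true conditional treatment hazard ratio of 0.618, and the accrual and follow-up above. Two samples of 100,000 patients were drawn per scenario. Scenario hazard ratios for age, KPS and MGMT were 1.3, 1.3, 0.6 (mild), 1.7, 1.6, 0.5 (moderate) and 2.5, 2.0, 0.4 (strong).

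| Scenario | (a) Treatment + MGMT, as planned | (b) Treatment, stratified (matches primary test) | (c) Treatment + MGMT, stratified |
|---|---|---|---|
| Mild | 0.617 | 0.623 | 0.611 |
| Moderate | 0.636 | 0.641 | 0.621 |
| Strong | 0.642 | 0.645 | 0.610 |

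Monte Carlo error is about 0.005 for each hazard ratio. Differences within a row are firmer, because the models share the same simulated patients.

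- Effect of dropping the strata, (a) − (c): 0.006, 0.015, 0.032.
- Effect of adding MGMT to the stratified model, (c) − (b): −0.012, −0.020, −0.035.
- Net difference a reader would see, (a) − (b): −0.006, −0.005, −0.003.

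The two changes pull in opposite directions and largely cancel. In the moderate case the visible difference of 0.005 hides an MGMT adjustment of 0.020.

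For the centre-volume model, suppose centre volume has no prognostic effect. The planned model then behaves like an unadjusted one. Unadjusted versus stratified is 0.628 vs 0.623 (mild), 0.653 vs 0.641 (moderate) and 0.667 vs 0.645 (strong). With no MGMT effect either, it is 0.634 vs 0.621 (moderate) and 0.652 vs 0.620 (strong). Here the whole difference from the primary analysis comes from the missing strata.

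**4. Against precision.** With 137.2 events the standard error of the log hazard ratio is about 2/√137.2 = 0.17. On that scale, dropping the strata from the MGMT model costs ln(0.617/0.611) = 0.010, ln(0.636/0.621) = 0.024 and ln(0.642/0.610) = 0.051. These are about 0.06, 0.14 and 0.30 of a standard error.

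**The case against.** The confirmatory test is correctly stratified by the randomisation factors, and the criticised models only support it. The article condenses a fuller plan: its Data Availability section refers to a separate analysis plan, which may stratify the Cox models and name the hazard ratio that accompanies the log-rank test. The multivariable list is open-ended, so treatment may be intended there. A less adjusted hazard ratio is also a different estimand, not a wrong one, and the shift is small against sampling error.

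Most of this stands, and it rules out several stronger readings that a reader might infer:

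- That every Cox model ignores age and KPS. The multivariable model contains both; the doubt is whether it contains treatment.
- That the MGMT-adjusted hazard ratio is diluted relative to the primary analysis. The matching comparison is (a) with (b), and the planned model is no closer to 1 (0.636 vs 0.641 in the moderate case), because adjusting for MGMT offsets the lost strata. Dilution relative to the primary test appears only if the added covariate is weakly prognostic, as centre volume may be.
- That the absence of a hazard ratio matched to the log-rank test is an error. A protocol article may leave that to the analysis plan.

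What the objection does not remove is that the article itself lists the variables of the two sensitivity models. An analysis plan that follows the list inherits the mismatch, and one that adds the strata departs from the published wording.

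**Conclusion.** The point holds as a minor one about interpretability. The mismatch between the stratified primary test and the two treatment-effect Cox models follows from the text alone and needs no assumption. Its numerical size does rest on assumed prevalences and prognostic effects: about 0.01 to 0.03 on the hazard ratio scale, towards 1, compared with the same model with strata. That is too small to change how the trial reads, but it is similar in size to the MGMT adjustment that the first model is meant to show. Whether the multivariable model includes treatment cannot be settled from the article.

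**What to change.** - Stratify both Cox sensitivity models by age group (<50 vs ≥50 years) and KPS class (70–80% vs 90–100%), so that each differs from the primary analysis only by MGMT or only by centre volume.
- Name treatment group among the variables of the multivariable Cox model.
- Optionally, report the treatment hazard ratio with 95% confidence interval from a Cox model stratified by the same two factors beside the log-rank test, as the reference for these models.

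Both factors are already recorded for randomisation. The change is to analysis wording only, needs no new data or sample size, and can be made before any OS comparison by arm.

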A simulation was performed to assess the non-inferiority of the slope of QoL scores over time in the two treatment groups, with a non-inferiority margin of 0.4 score points (using the quarter as the time unit). The simulation incorporated survival status based on the previously stated assumptions and assumed a compound symmetry for the correlation structure of QoL scores across time points, with a correlation coefficient of 0.7. The results indicate that a total of 170 evaluable subjects in the mITT population will provide approximately 80% power to test for non-inferiority of QoL (linear mixed-effects model with QoL score as dependent variable, random patient intercept, and treatment group + time as independent variables, 95% confidence interval of the interaction between time and treatment, 1000 Monte Carlo replications, mean power 83%, Monte Carlo error 1.2%).

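### The co-primary QoL slope model leaves out age group and KPS class; if QoL slopes differ by stratum, power and the false non-inferiority rate both suffer, by an amount the article does not allow one to fix

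*Protocol article*

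**What the plan says.** The Randomization section announces "Stratification will occur based on two criteria": age below 50 versus 50 and over, and preoperative KPS 70–80% versus 90–100%. The Primary outcome section carries both factors into the survival analysis: "The log-rank test will be stratified by age group" and by KPS class.

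The co-primary QoL analysis in the same section is a linear mixed model with "QoL score as dependent variable, random patient intercept, treatment group + time as independent variables". The slope difference between the arms is then assessed by "estimating a 95% confidence interval of the interaction between time and treatment". Non-inferiority is judged "using a non-inferiority margin of 1.6 score points per year". The model has no stratification factor, no factor-by-time term and no random slope. The Sample size calculation section uses the same model for its simulation (170 evaluable patients, correlation 0.7 under compound symmetry, margin 0.4 points per quarter, mean power 83%). The Secondary outcome variables section applies analogous models to the other QoL domains.

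**The concern.** The tested quantity is a difference between two slopes, against a tight margin. Patients with lower KPS may lose QoL at a different rate from patients with higher KPS. If so, part of the slope variation between patients is explained by a known design factor that the model ignores.

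This has two consequences.

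- **Standard error too small.** A random-intercept model treats all patients in an arm as sharing one slope. Patients followed longest carry most of the slope information, and their KPS mix varies by chance between arms even when the strata are balanced at randomisation. The model's standard error does not reflect this.
- **Bias.** The arms are planned to differ in survival (medians 17 and 27.5 months). If KPS also predicts survival, the share of slope information coming from low-KPS patients differs systematically between the arms.

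The QoL test is one of the two conditions for declaring overall superiority. Its planned power is only a little above 80%.

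**Working it through.** **Inputs from the article.** 170 evaluable patients (85 per arm); median OS 17 and 27.5 months; 36 months' accrual plus 36 months' follow-up; quarterly QoL; compound symmetry 0.7; margin 0.4 points per quarter; bound of a 95% confidence interval; 1000 replications; power 83%.

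**Assumptions not in the article.** Exponential survival; 40% of patients in the low KPS class; 85% aged 50 or over; the low-KPS (or older) group declines faster; true treatment slope difference 0 for power and −0.4 per quarter for false non-inferiority. No QoL SD is given, so it was solved to give about 83% power, which yields 19.8. The 83% is therefore calibrated, not independently reproduced.

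**Checks on the stated figures.** Margin: 4 × 0.4 = 1.6 points per year, so the two sections agree. Monte Carlo error: √(0.83 × 0.17 / 1000) = 1.19%, matching the stated 1.2%.

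**Simulation.** Stratified permuted blocks, visits until death or end of trial, REML random-intercept fit. Non-inferiority is declared if the lower 95% bound exceeds −0.4. Power of the model as written:

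| KPS-class slope difference (points/year) | Equal survival | Low-KPS hazard ratio 1.5 |
|---|---|---|
| 0 | 82% | 84% |
| 1 | 82% | 79% |
| 2 | 81% | 78% |
| 3.2 | 77% | 72% |
| 4 | 75% | 68% |
| 6.4 | 69% | 57% |

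Repeat runs with slightly different set-ups gave 73–76% (equal survival) and 68–73% (hazard ratio 1.5) at 4 points per year.

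With both factors and their interactions with time added, power was about 82% with equal survival and 83% with the hazard ratio of 1.5, whatever the slope difference. Across all runs it was about 80–84%. With no slope difference it was 81.8%, against 82.5% as written: a cost of 0.7 points. With main effects only, power in the equal-survival scenarios moved by at most about 0.6 points.

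For age group alone, power as written was 81.3% at 1.6 points per year and 79.0% at 3.2. With both factors differing, it was 80.1% and 74.8%.

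**Why.** Let b be the bias, SE the average model standard error and SD the empirical standard deviation of the estimate, all per quarter. Then power ≈ Φ((0.4 + b − 1.96·SE)/SD), and false non-inferiority ≈ Φ((b − 1.96·SE)/SD).

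- 2 points/year, equal survival: SE 0.1389, SD 0.1523, b ≈ 0. Power ≈ Φ((0.4 − 0.2722)/0.1523) = Φ(0.84) ≈ 80%. False non-inferiority ≈ Φ(−0.2722/0.1523) = Φ(−1.79) ≈ 3.7%.
- 3.2 points/year, equal survival: SE 0.1399, SD 0.170, b ≈ 0. Power ≈ Φ((0.4 − 0.2742)/0.170) = Φ(0.74) ≈ 77%. False non-inferiority ≈ Φ(−1.61) ≈ 5.4% (simulated 5.2%).
- 3.2 points/year, hazard ratio 1.5: b = −0.043, SE 0.1367, SD 0.1548. Power ≈ Φ((0.357 − 0.2679)/0.1548) = Φ(0.58) ≈ 72%. False non-inferiority ≈ Φ((−0.043 − 0.2679)/0.1548) = Φ(−2.01) ≈ 2.2%.
- With the terms added, equal survival: SE 0.1401, SD 0.1409, b ≈ 0. Power ≈ Φ((0.4 − 0.2746)/0.1409) = Φ(0.89) ≈ 81%. SE and SD now agree.

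At 4 points per year with equal survival, simulated false non-inferiority was about 7.5% as written (5.9–7.6% across runs) against 2.0% with the terms. With the survival link, the bias against ATL offsets the short standard error, and the rate was about 2–4%.

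**Sensitivity.** With 20% low KPS, power as written was 82%, 79% and 73% at 1.6, 3.2 and 6.4 points per year. On the visit schedule of Table 1, with the SD recalibrated to 18.1, it was 81%, 77% and 70%.

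**The case against.** The strongest reply is that nothing in the article says QoL slopes differ by KPS class or age, or by how much. That stands, and it limits the point. A reader might infer that the omission alone takes power well below 83%. It does not. A KPS-class difference equal to the margin (1.6 points per year) costs about 1 point of power with equal survival, which is hardly distinguishable from simulation noise. A large loss needs a difference near 4 points per year, 2.5 times the margin, or a survival link as well.

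A reader might also infer that only power is at risk because false non-inferiority stays near 2%. That holds only when shorter survival at low KPS biases the comparison against ATL. Without that link the rate rises.

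Third, copying the log-rank stratification would mean adding main effects, and these change nothing here. This is correct; the case rests on the time interactions.

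Fourth, slope variation unrelated to the strata is a wider weakness of a random-intercept model. With an individual slope SD of 0.4 per quarter, power is about 74–77% with or without the stratum terms. So one cannot claim that these terms restore power in general. That is a separate point, which would need a random slope.

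Finally, an analysis plan not shown could add covariates. But the article writes this model out for a confirmatory endpoint and bases its power figure on it.

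**Conclusion.** The point holds as a conditional one. The model for the co-primary QoL test omits the two factors used for randomisation and for the OS test, and it is exposed if QoL slopes differ by those factors. For modest differences in KPS-class slope with equal survival the loss of power is negligible to small. It becomes material at about 4 points per year, or earlier if low KPS also shortens survival. The understated standard error matters as much as the power, because it can raise the chance of wrongly declaring non-inferiority.

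These sizes rest on the back-solved SD, the assumed KPS share and the assumed hazard ratio, none of which the article supplies. The direction of the effects and the near-zero cost of the remedy do not depend on the exact values within the ranges tried.

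**What to change.** Add age group and KPS class, each with its interaction with time, as fixed effects in the co-primary QoL model and in the analogous secondary QoL models, and state this before any outcome data are seen. This means four extra parameters on variables already collected for randomisation. The cost is under 1 point of power if slopes do not differ by stratum. Main effects without the time interactions would not serve. Whether to add a random slope for variation unrelated to the strata should be decided separately.

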### Secondary outcome variables

Secondary endpoints will be analyzed descriptively in the mITT population, if not otherwise stated. QoL will be assessed using the standardized and validated EORTC QLQ-C30 and QLQ-BN20 questionnaires. These questionnaires include health-related QoL questions scored on a nominal scale (primarily values from 1 to 4). The responses to individual questions will be recorded for analysis, and questions related to the same QoL dimension (e.g., emotional well-being) will be aggregated to generate an overall score for that dimension, following the scoring manual.

The scores for different QoL dimensions in each treatment group will be analyzed descriptively based on repeated assessments throughout the trial. Analogously to the analysis of the co-primary endpoint, linear mixed-effects models will be applied to the data to evaluate potential differences in the trends of QoL measurements over time between the treatment groups.

PFS will be summarized in the same manner as OS. Median PFS time estimates and associated 95% confidence intervals will be reported. The analysis of PFS will also be performed, similarly to the primary endpoints, within the ITT- and PP-populations as well as in the small population of patients with IDHmut diffuse high-grade glioma.

Neurocognitive function will be analyzed on both the group and the individual level. Group-level analyses will be conducted using multivariable linear mixed-effects models with post hoc tests to evaluate group differences. The side of surgery (left/right) will serve as a primary independent variable alongside the study arm.

At the individual level, both objective and subjective test data will be analyzed based on categories of impairment relative to test norms at each time point. Changes will be considered individually significant if they indicate a shift between performance categories across the three assessments (*p* < 0.1).

